### Data privacy

After performing a thorough data protection impact assessment, the local hospital security information and privacy officers granted permission to perform the study. This was also validated by the ethics review board. The data protection impact assessment describes a data management plan conforming to the European General Data Protection Regulation. To protect the data privacy of the participants, all data are pseudonymized. Only the researchers have access to the sensor data, and only the Principal Investigator has access to personal information of participants (ie, names, contact information, etc). They have all signed processing agreements. Second, the Google servers storing the data are only located within the Netherlands; hence the data does not leave the country, therefore conforming to Dutch law. This is done to have a clear data infrastructure both legally and technically to explain to participants.

### Data characteristics and preparation

The data first undergoes a process involving resampling and artifact removal. In our experience with Fitbit smartwatches, the heart rate is nonuniformly sampled, with a prevalent rate of 0.2 Hz. Therefore, the heart rate is resampled to once per 5 seconds. The step counter is sampled once per minute.

Artifacts involving samples with numerous consecutive constant values are removed, if more than 12 consecutive constant values (equivalent to 1 minute of heart rate samples) are detected. This 1-minute threshold was chosen based on visual inspection, which revealed that heart rate patterns typically occur in the order of minutes, often spanning 10–20 minutes. For sequences with fewer than 12 consecutive missing values, linear interpolation is applied. From the cleaned time series, smaller segments, denoted as windows, are extracted and employed as input for a machine learning model. This process involves a sliding window and windows containing time gaps are excluded. Windows have 2 design considerations: the window size, which determines the number of samples within a window and defines its dimensionality, and the stride, which establishes the step size dictating the shift between windows.

Although the cardiovascular condition of each subject is known, it is unknown in which specific windows these conditions manifest themselves. This is owing to the paroxysmal nature of atrial fibrillation and the variable symptoms of heart failure, which can be influenced by factors like medication adjustments, dietary changes, and the disease’s progressive course. In other words, the subject label is known, but the individual window labels are unknown. This is visually represented in Figure 2a, where the subject label is depicted by the blue/red colors and the unknown window labels are indicated by black dotted lines.

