### Data show large inter-subject variability

Nonoverlapping 1-hour windows are used to segment heart rate and step counter time series data from 6 subjects. To visualize this high-dimensional data, UMAP^11^ is employed to reduce the data to 2 dimensions while maintaining as much structure as possible. The resulting embedding is displayed in Figure 5, where the distribution of the 2-dimensional UMAP samples are illustrated per subject.

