**Figure 5 fig5:**
[figure not shown]
Visualization of heart rate windows (upper image) and step windows (lower image) of 6 subjects. Each window has data of 1 hour (720 time points for heart rate, 60 for steps, respectively). Each high-dimensional window is mapped to a 2-dimensional (2D) location using UMAP.^11^ The contour curves illustrate the distribution of the 2D UMAP samples for each subject, with each color representing 1 of the 6 subjects.

When there is little overlap between subjects, finding a shared pattern among them becomes challenging, making it difficult for a model to learn. As a result, the performance of a machine learning model could be impacted as, during testing, a subject can significantly deviate from the subjects on which the model was trained.

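### The artifact rule deletes heart rate that stays constant for just over a minute and drops every window containing the gap; the stated reason does not show a flat minute is artifact, and the loss may differ by class

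*Protocol article*

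**What the plan says.** All the relevant rules stand in the protocol article, Methods, under Data characteristics and preparation.

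- Sampling: "the heart rate is resampled to once per 5 seconds".
- Deletion: long stretches of one repeated value are treated as artifact and removed "if more than 12 consecutive constant values (equivalent to 1 minute of heart rate samples) are detected".
- Reason for the cut-off: "visual inspection, which revealed that heart rate patterns typically occur in the order of minutes, often spanning 10–20 minutes".
- Repair: "For sequences with fewer than 12 consecutive missing values, linear interpolation is applied".
- Consequence: "This process involves a sliding window and windows containing time gaps are excluded".

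Window length is not fixed for the final model. Algorithm validation names window parameters as hyperparameters to be tuned in the leave-p-subjects-out cross-validation (LPSOCV). The 1-hour window appears in the preliminary results: "Nonoverlapping 1-hour windows are used to segment heart rate and step counter time series data from 6 subjects".

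**The concern.** The rule decides what is artifact from one property, a heart rate that does not change for just over a minute. That property belongs to the signal the study wants to classify on. A frozen sensor and a truly steady rate look the same to it. The justification concerns how long informative patterns last. It does not address how long a true heart rate, recorded on this device, can stay at one value.

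If true steady stretches are removed, the model is trained and tested on the more variable part of each recording. If steadiness differs between groups, the number and kind of windows per subject also differ by class. This can reach the decision rule. Planned machine learning approach sets a threshold on the number of positive instances in a bag, so fewer windows directly make a positive call harder. The prediction step of Box 1 uses a percentage; there, plain loss of windows largely cancels, but selective loss still changes which windows are counted. In either case part of the apparent performance could come from the filter.

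**Working it through.** **Inputs from the article.** Sample spacing 5 s; deletion of runs of more than 12 equal values; interpolation of fewer than 12 missing values; exclusion of windows with gaps; 720 heart-rate points per hour (Figure 5 caption).

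**The article's own figure.** 12 samples × 5 s = 60 s, which reproduces the stated 1 minute. Likewise 3600 s / 5 s = 720 points.

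**The chain of rules.** The shortest deleted run is 13 samples (13 × 5 = 65 s). The longest interpolated gap is 11 samples. Since 13 > 11, a deleted run is never filled, and every window containing it goes.

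**Cost of one deleted run.** With window length W and run length L in samples, and stride 1, the window starts lost are W + L − 1. For L = 13:

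- 1-hour window: 720 + 12 = 732 starts = 61 min
- 20-minute window: 240 + 12 = 252 starts = 21 min
- 10-minute window: 120 + 12 = 132 starts = 11 min

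**How often could true signal trigger the rule?** The article gives no frequency, so this rests on assumptions.

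*Assumption A.* Each value equals the one before it with probability p, independently. The chance that a window of n samples holds a run of 13 or more is close to 1 − exp(−λ), with λ = p^12 × [1 + (n − 13)(1 − p)]. For n = 720 and p = 0.6: p^12 = 0.002177, the bracket is 1 + 707 × 0.4 = 283.8, λ = 0.618, and the result is 46%. The exact Markov-chain values are:

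| p | 10 min | 20 min | 1 hour |
|---|---|---|---|
| 0.4 | 0.1% | 0.2% | 0.7% |
| 0.5 | 1% | 3% | 8% |
| 0.6 | 9% | 18% | 46% |
| 0.7 | 38% | 64% | 96% |
| 0.8 | 85% | 98% | about 100% |

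*Assumption B.* An artifact-free AR(1) heart rate rounded to whole bpm, with correlation time 60 s (lag-1 correlation exp(−5/60) = 0.92). Simulated share of windows holding such a run (20,000 series per row):

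| SD (bpm) | 10 min | 20 min | 1 hour |
|---|---|---|---|
| 1 | 39% | 64% | 96% |
| 1.5 | 4% | 8% | 23% |
| 2 | under 1% | 1% | 3% |
| 3 | 0% | 0% | about 0% |

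The correlation time matters as much as the SD. At SD 1.5 bpm the 1-hour loss is about 0.3% with 20 s and about 87% with 120 s. Both tables count only runs lying wholly inside a window; windows that overlap part of a deleted run are lost too, so the figures are slightly low.

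**Could loss differ by class?** Study design and data collection defines the reference group as having no medical history and no medication, so drugs that affect heart rate can occur only in the AF and HF groups. In Table 1, 16 of 25 reference participants (64%) are aged 18–39, and 17 of 22 AF participants (77%) are 65 or older. The groups therefore differ in things that may bear on steadiness. None of this gives a loss by group.

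**The case against.** The threshold is stated in advance, has a stated reason and is applied identically to all groups. A journal article condenses; wear checks and tables of data loss may sit in the full protocol, and their absence here is no fault. The 1-hour window comes from a six-subject visualisation, while the final window size is tuned, and shorter windows lose far less. The large percentages depend on the assumed SD and correlation time: the same model gives almost no loss at 3 bpm. Box 1's percentage rule partly corrects for unequal numbers of windows. The Discussion also favours preselecting windows such as acceleration-deceleration curves, in which the rate changes by construction.

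All of this limits the size of the claim, and it stands. It does not remove the fault: the stated reason does not support the stated cut-off, and an identical rule need not act equally on groups that differ in steadiness.

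A reader might go further and infer that steady rhythms are in fact being lost and that window loss depends on disease. The article does not support that. It reports neither how often such runs occur nor window loss by group. The smaller standard deviation reported for AF describes the spread of rescaled light-activity curves in 7 persistent-AF and 15 healthy subjects; it says nothing about constant runs, or about HF. Nor can the argument rest on paced rhythms: pacing is never mentioned, and its absence from the exclusion list does not show that paced patients are enrolled.

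**Conclusion.** The concern holds as a risk. As written, the rule removes any constant run of 13 or more samples on constancy alone, cannot restore it, and discards each window containing it; the reason given does not show that such runs are artifact. True low-variability signal can therefore be lost, and the loss may differ between classes, in an unknown direction.

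The size cannot be stated from the article. Under the assumed whole-bpm AR(1) signal with a 60-second correlation time, the loss of 1-hour windows runs from about 96% at SD 1 bpm to about 0% at SD 3 bpm. Those figures describe the assumed signal and not this study. They show only that modest differences in steadiness can move the loss from negligible to nearly complete, so it should be measured. This is a worthwhile, inexpensive improvement to the plan.

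**What to change.** 1. Treat the run-length threshold as a preprocessing hyperparameter, alongside the window parameters, in LPSOCV.
2. Compute the fraction of data and of windows removed by this rule, per subject and per class, and test whether that fraction alone predicts class.
3. Repeat the final model without the rule, or with a clearly longer run length, as a sensitivity analysis. If performance depends on the rule, limit the conclusion accordingly.

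Step 2 should be read together with step 1: if the removed fraction predicts class, tuning on performance could favour a threshold for that very reason.

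Masking the runs and keeping the windows is another option, but that is a design preference and is not needed to meet the point.

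The cost is a change to the preprocessing code and one or more extra model runs; no new data are needed. The downside is that some true sensor-freeze segments stay in during the sensitivity run.

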**Figure 2 fig2:**
[figure not shown]
Pipeline for the study’s proposed approach. **a:** Segmentation of the time series of each subject (1 healthy and 2 atrial fibrillation) using a sliding window. Only the label of the entire subject is available, instead of each individual window. **b:** The windows are inputs to an autoencoder and are compressed to a smaller (2-dimensional for illustrative purposes) representation. **c:** The compressed representation is used to train a multiple-instance classifier that can distinguish between healthy, atrial fibrillation, or heart failure). AF = atrial fibrillation.

### Planned machine learning approach

Our planned machine learning approach is tailored to operate in this setting through a 2-stage process. To learn informative patterns/features directly from the input data, despite the lack of labeled windows, the first stage involves using self-supervised learning. A commonly used self-supervised learning technique involves compressing the input windows to a lower-dimensional representation and then reconstructing the original input from this compact representation, as depicted in Figure 2b.^7^^,^^8^ Instead of reconstruction, another technique is to forecast future time points of the input data.^9^ The second stage involves multiple-instance learning (MIL). MIL, depicted in Figure 3 and more elaborately explained in Box 1, is suitable for data where a single prediction is made collectively on a group of samples (known as a “bag”) instead of predicting on individual samples (known as “instances”). MIL techniques align well with our time series data, where during the training phase only 1 label related to the subject (bag label) is known while the individual labels of the compressed windows (instance labels) remain unknown. In the testing phase the primary objective is to predict 1 clinical outcome for each subject. The key concept in MIL is that each bag of instances is labeled as positive (heart disease) if it contains a certain amount of positive instances and negative (healthy) if it contains no positive instances (only negative instances). Although traditional MIL approaches often classify a bag as positive even with just 1 positive instance, we aim to minimize false-positives by setting a threshold on the number of positive instances required to label a bag as positive. This threshold will be determined through hyperparameter tuning. Thus, instead of learning a model that predicts the cardiovascular outcome of individual instances, we are learning a model that predicts the outcome of a bag of instances.

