Box 1. A simple multiple-instance learning exampleMIL is elaborated with an example in 3 steps.**Initial setup** Under traditional supervised learning, each window must be annotated to train a machine learning model. However, in our MIL setting (Figure 3), only the bag label is known for the entire set of windows related to a subject. A bag label is considered negative if none of the subject’s individual samples are associated with heart disease, indicating that the subject is not affected by it. Conversely, a bag label is positive if a certain amount of the subject’s samples is linked to heart disease.**Learning** The algorithm then learns a model based on the bag-level labels only. The goal of the MIL algorithm is to learn a model that can correctly predict the bag-level labels given the instances in each bag. By training on the bag-level labels, the MIL algorithm can capture patterns and relationships within the data that help identify the presence or absence of heart disease. Note that the decision boundary produced by the model in Figure 3 is not ideally suited for classifying individual windows, which is expected, as it did not use this information. However, if a sufficient number of windows are classified accurately, the correct bag label can still be predicted. This is accomplished during training by aggregating these accurate classifications using methods like majority voting, or by setting a threshold for the minimum number of positively predicted windows needed to assign a positive bag label.**Prediction** Once the model is trained, it can predict the label of a new bag by examining the instances in the bag. If the model predicts that a certain percentage of instances in the bag are positive defined by the threshold, the bag is classified as positive (heart disease) and negative (healthy) otherwise. By analyzing the presence or absence of positive instances within the bag, the MIL algorithm can make predictions on a bag level, providing insights into the subject’s condition.

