**Figure 4 fig4:**
[figure not shown]
Our leave-p-subjects-out cross-validation strategy consists of the following: On the left, cross-validation folds are illustrated using 3 subjects with corresponding subject number. Green and blue represent training and validation subjects, respectively. On the right, a single fold is expanded and additionally illustrates the internal and external test sets. Each row corresponds to a subject, and the dotted squares within each row represent windows. The yellow external test block encompasses entire subjects and their corresponding data points that have not been encountered by the model. Meanwhile, the dark yellow internal test block consists of unobserved data points, representing the final 20% measurements of the time series from subjects already encountered during model development.

Machine learning models are sensitive to the distribution of classes. To mitigate potential bias owing to different class distributions in each fold, we incorporate stratification during the cross-validation process. This ensures that the ratio of nonarrhythmic, atrial fibrillation, and heart failure subjects remains approximately consistent and that the influence of inconsistent class distribution across different folds is minimized.

However, Fitbit time series data exhibit inter-subject variability resulting from individuals’ distinct physical attributes,^10^ making the development of a universally effective model for “new” subjects challenging. In order to examine the effect of inter-subject variability, we will assess the model on 2 distinct test sets. The first is an external test set that consists of subjects not previously encountered, randomly selected to make up 20% of the total subjects, with an equal number from each class. This allows us to evaluate the model’s generalization capabilities. The second test set is an internal one, encompassing the final 20% of data from subjects previously encountered by the model. This segment of data was excluded during the cross-validation phase and serves as a baseline, as it minimizes the influence of inter-subject variability, providing a reliable reference for comparison.

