Parameters not directly learned by the machine learning model, such as window parameters, are termed hyperparameters. Since optimal values are typically unknown in advance, multiple options are examined during LPSOCV, and the best-performing one, with the best average performance over all folds, is chosen for the final model; a process known as hyperparameter tuning.

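### The bag threshold is a count of positive windows in two places and a percentage in a third; a tuned count would not carry over to the shorter internal and longer external test bags.

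*Protocol article*

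**What the plan says.** Three places in the protocol article describe the rule that turns window predictions into a subject's label.

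- Planned machine learning approach: false positives are to be limited by "setting a threshold on the number of positive instances required to label a bag as positive". No value is given: "This threshold will be determined through hyperparameter tuning".
- Box 1, Learning: window predictions are aggregated by majority voting or by "setting a threshold for the minimum number of positively predicted windows needed to assign a positive bag label".
- Box 1, Prediction: a new bag is called positive when "a certain percentage of instances in the bag are positive defined by the threshold".

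The first two are counts and the third is a proportion. Nothing relates them or scales the count to bag length.

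Box 1 defines the bag as all of a subject's windows, and the planned approach makes one prediction per subject at test. On tuning, Algorithm validation says that "multiple options are examined during LPSOCV, and the best-performing one, with the best average performance over all folds, is chosen for the final model". The internal test set is described as "encompassing the final 20% of data from subjects previously encountered by the model", and that segment is kept out of cross-validation. The Figure 4 caption says the external test set contains entire subjects. Under Data characteristics and preparation, "windows containing time gaps are excluded".

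**The concern.** A count and a percentage are the same rule only when every bag has the same number of windows. Here bag sizes differ by design between tuning, internal test and external test. They also differ between subjects, because windows with gaps are dropped. A count tuned on one bag length is a different rule on another.

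At stake is the comparison between the two test sets. The article uses it to examine inter-subject variability and treats the internal set as the baseline. Under a fixed count, the short internal bags would rarely reach the threshold and the long external bags would reach it too easily. The two sets of results would shift in opposite directions with an unchanged window classifier, and that shift could be read as an effect of unseen subjects. On external bags the count would also work against its stated purpose of limiting false positives.

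**Working it through.** The article gives no threshold value and no performance target, so there is no figure to reproduce.

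**Step 1: bag lengths (from the article).** Let L be a subject's number of valid windows over the 3 months, spread evenly over time.
- Tuning bag: 0.80L. Internal test bag: 0.20L. External test bag: 1.00L.
- Internal/tuning = 0.20/0.80 = 0.25. External/tuning = 1.00/0.80 = 1.25.

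**Step 2: what a tuned count becomes.** Write the count as k = f × 0.80L.
- Share of an internal bag: k/0.20L = 4f.
- Share of an external bag: k/1.00L = 0.8f.
- If f > 0.25, then 4f > 1 and no internal bag can be positive.

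These results need no assumption about window size or positive rates.

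**Step 3: illustration (assumptions).** Take 90 days of complete, non-overlapping 1-hour windows. The article uses 1-hour windows only in a preliminary visualisation. Then L = 90 × 24 = 2160, giving bags of 1728 (tuning), 432 (internal) and 2160 (external). A count of 173, which is 10% of the tuning bag, is 173/432 = 40% of an internal bag and 173/2160 = 8% of an external bag.

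**Step 4: operating characteristics (assumptions).** Each subject's number of positive windows is beta-binomial. The count k maximises sensitivity + specificity on the tuning bags and is then applied unchanged.

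Spread scenario: reference subjects have a mean positive-window rate of 10% (SD 0.03), patients 25% (SD 0.06). The tuned count is k = 274, or 15.9% of the tuning bag.

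| Bag | Windows | k as share of bag | Sensitivity | Specificity |
|---|---|---|---|---|
| Tuning | 1728 | 15.9% | 0.94 | 0.96 |
| Internal | 432 | 63.4% | 0.00 | 1.00 |
| External | 2160 | 12.7% | 0.99 | 0.81 |

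The same threshold held as a percentage gives sensitivity 0.93 to 0.94 and specificity 0.95 to 0.96 on all three lengths.

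Six further settings (reference/patient rates 5/20%, 10/30% and 17.5/44%, each with beta precision 20 and 50):

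| Rates, precision | k | Internal sensitivity | Specificity, tuning → external |
|---|---|---|---|
| 5/20%, 20 | 167 | 0.033 | 0.853 → 0.782 |
| 5/20%, 50 | 189 | 0.000 | 0.950 → 0.881 |
| 10/30%, 20 | 305 | 0.000 | 0.872 → 0.770 |
| 10/30%, 50 | 323 | 0.000 | 0.963 → 0.872 |
| 17.5/44%, 20 | 503 | 0.000 | 0.903 → 0.772 |
| 17.5/44%, 50 | 514 | 0.000 | 0.979 → 0.873 |

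Internal sensitivity is 0 to 0.03 and external specificity drops by about 7 to 13 points. With a percentage threshold in the same six settings, sensitivity and specificity stay within about 1 point across bag lengths.

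**The case against.** The strongest reply is that the article does not really plan a count. The one sentence on classifying a new bag uses a percentage and refers back to the same threshold. Majority voting, offered beside the count, is itself a proportion. Box 1 is presented as a simple example, and a condensed article may leave the exact rule to a fuller document. This establishes that the harm is conditional: it arises only if the count is what gets implemented. It does not remove the contradiction. The count also stands in the description of the planned method itself, which points to Box 1 for the fuller explanation. The article fixes the rule in two incompatible ways, which is different from omitting it.

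A second reply is that whole-recording test bags are an inference, since the preliminary MILES analysis grouped data by week. Weekly bags would largely remove the length difference. But the planned approach describes one bag per subject and does not adopt weekly bags.

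A reader might also infer that a count ruins the external test outright. Without between-subject spread and with rates of 10% and 20%, a count of 199 does give an external specificity of about 10%. That result comes from placing the threshold near the 97.5th percentile of the reference distribution. The article instead tunes for best average performance. The count that maximises sensitivity + specificity in that scenario is 251, and its external specificity is 99%. External results under a count are miscalibrated, not useless.

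Nor do the documents support saying that good wearers are called diseased and poor wearers healthy. No wear-time distribution is given, and the calculations assume complete recordings. Only the direction is clear: more valid windows make a positive label more likely.

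**Conclusion.** The contradiction is real and concerns the rule that produces each subject's predicted label. Given one bag per subject, the length ratios of 0.25 and 1.25 follow from the article's own data split.

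If the count is implemented, internal sensitivity collapses: to about 0 in every assumed scenario, and necessarily to 0 when the tuned count exceeds 25% of a tuning bag. External specificity falls moderately, from about 96% to 81% in the spread scenario and by about 7 to 13 points in the other six. The internal-versus-external contrast would then partly measure bag length, and variation in wear time would add a bias in the same direction. If the percentage is implemented, none of this follows.

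The sizes rest on assumed 1-hour windows, complete 90-day recordings and assumed positive-window rates and spread.

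**What to change.** In the planned machine learning approach and in both the Learning and Prediction steps of Box 1, define the threshold as the percentage of a bag's valid windows predicted positive, and remove the two statements in terms of a number.

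Alternatively, keep a count but use bags of equal size in tuning and in both test sets. Fixed-duration bags, as in the weekly preliminary analysis, would do this approximately. Because dropped windows still make their sizes vary, they would need to be cut to the same number of valid windows for a count to be exact. If fixed-duration bags are used, say how the bag results combine into the single prediction per subject.

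The percentage option costs a wording change and needs no new data. It also lets the internal set serve as the baseline the article intends.
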